**Figure 2 figure2:**
[figure not shown]
Flow diagram of the The Cancer PEPSONE study.

### Intervention

The intervention is a psycho-educational program for the family and its network members. The authors developed the program based on clinical experience, previous research, and the theoretical framework previously outlined. It was pilot-tested by two of the authors and thereafter, all the authors discussed and modified the program to its final structure.

The parents in the intervention families decide who in the family and which network members would participate in the program. The program is conducted in the families’ homes, or else where they choose, by one of three clinical psychologists, all of whom are experienced in working with families and children in crisis. It lasts for approximately 3 hours. None of the researchers are involved in the intervention that contains the elements described in Textbox 1.

Elements included in the intervention.Welcome and introduction (10-15 minutes): The psychologist leading the meeting introduces herself and presents the content of the program before the participants introduce themselves. The goals of the program are (1) to emphasize the importance of network support; (2) secure social network support for cancer families over time; (3) share knowledge to make each other wiser.Psycho-education (approximately 1 hour): In this part, the psychologist has a teaching session focusing on the following areas: (1) the consequences of living with a cancer diagnosis in the family for the sick and the healthy parent, and with a special focus on the children; (2) general reactions and the needs of both the children and the adults; (3) common useful coping strategies for crisis; (4) the importance of social network support, focusing on what is social network support for families in crisis, and what do we know about helpful network support; (5) the importance of “openness” and communication between the family and the network; (6) what can social networks do, and different types of social support (eg, emotional, practical, information, and economical support); (7) how to sustain network support over time: the importance of distribution, and the coordination of support.Discussion (approximately 1.5 hours): Based on the teaching session, the goal of the discussion is to enhance the family and its network members’ understanding of the value of open communication about the family’s need for social support and the network members’ ability and willingness to give such support. The psychologist facilitates the discussion based on the experiences from previous support giving/receiving processes between the family and the network, the family’s current needs and what is the network able and willing to do as well as coordination of the network support.Summing up and closing (10 minutes): The psychologist sums up the main points from the teaching session and the discussion.

A detailed procedure for the intervention is developed and reviewed by the intervention psychologists together with the authors securing that the intervention is performed in the same manner for all families. After the meeting, the psychologists fill out a form with information about how the intervention went according to the protocol, who attended the meeting (roles/relations), the themes discussed, and a short field note to record any observations about the context and impressions arising from the meeting. All participants in the intervention also fill out an evaluation form on how they experienced the psycho-education.

### Eligibility Criteria

The study contains 3 samples. Sample 1 and 2 (n=60) consist of 30 families in the intervention group and 30 in the control group. These samples include the healthy parent and one child from each family. The inclusion criteria for these families are (1) a healthy parent having a partner or spouse diagnosed with cancer within the last five years and treated for cancer and (2) one child in every family, aged 8-18 years old, living with a parent who has cancer. With multiple children in the family, the oldest child who is willing to participate will be recruited. The parents in the intervention group ask the number of adult network members (mean 7, limited to 15 network members, N=210) if they want to participate in the intervention. This group of adult network members makes up Sample 3. The inclusion criteria for these network members are (1) extended family members, friends, neighbors, and work colleagues of the parents, (2) ≥18 years, and (3) living nearby the family.

The exclusion criteria for the study are (1) healthy parent not living with the ill parent or the ill parent has died, or having a serious disease, (2) children <8 years old, not living with ill parents, serious disease themselves, and (3) network members living >2 driving hours from the family.

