Several studies have emphasized the importance of social support for physical and mental health, for quality of life, as well as for coping with and recovering from cancer [28-31]. Nonetheless, cancer patients still experience disruptions in their social lives as well as unhelpful help or a lack of social support, especially over time [8,32]. Cancer patients’ main concern regards caring for their children, and in particular they want to protect their children and maintain an ordinary everyday life [20,33,34]. A number of these parents express that they are dependent on help from their social network to sustain their regular everyday life, and call for more and prolonged support to uphold their own parental capacity and avoid “hitting the wall” [7,35]. These families often find it difficult to ask for the help and support they actually need and they often experience that help and support drop shortly after the diagnosis and their network withdraws [7-9].

Previous research has found that network members surrounding families in crisis are generally positive in providing support but that they are often insecure about how to help. They report being afraid to say or do the “wrong things”, of intruding on the family, or they may assume that their contributions are unimportant or that the family copes adequately on its own [7,8,36]. Network members claim that by acknowledging support efforts and providing various strategies, professionals can facilitate better and more prolonged network support [36].

Most studies of social support related to cancer are descriptive, documenting the importance of social support for physical and psychological health as well as for quality of life [32]. Intervention studies on enhancing social support lag far behind, and are mostly directed to cancer patients, especially breast cancer, focusing on different kinds of support groups [37,38]. Intervention studies related to parental cancer and dependent children are lacking, as are intervention efforts aimed at enhancing social support for children and families members [39]. However, Hogan’s review [38] provides support for the overall usefulness of different social support interventions.

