#### Recruitment

Participants are recruited nationwide using a wide-ranging recruiting strategy including information acquired through hospitals and primary healthcare, brochures, and different websites. Families are also recruited through the Norwegian Cancer Society, the Montebello Cancer Center, child responsible healthcare professionals in hospitals, cancer coordinators in primary healthcare, and resource nurses in cancer care and palliation.

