##### Outcome Measurements

The questionnaire for the healthy parents includes the information shown in Textbox 2. The questionnaire to the children includes the information shown in Textbox 3. The questionnaire set to the network members includes the information shown in Textbox 4.

Information included in the questionnaire for the healthy parents.Demographic data about the healthy parent: age, gender, education, social status, children, employment status, and income.Demographic and medical data about the sick parent: age, gender, type and degree (metastasis) of cancer, months since diagnosis, type of treatment, and months of treatment and current treatment status.The Crisis Support Scale (CSS) [48] and the Assistance Questionnaire-Receivers of support (AQR) [49] measure social support. CSS is a short scale for measuring social support after a crisis has occurred, consisting of 7 questions with a rating scale from 1 (never) to 7 (always). All items are summed for a total mean score, where a higher total score indicates more received support. The scale appears to be very robust and to have satisfactory psychometric properties [48]. AQR measures adults’ experiences and need for 9 different types of social support related to the situation caused by the cancer. The instrument was developed by Dyregrov et al [49] and is applied on comparable populations both nationally and internationally.The Quality of Life Scale (QOLS-N) is used to measure the healthy parent’s quality of life [50]: This instrument measures an individual’s overall satisfaction with life based on different life domains. It contains 16 items scored on a 7-point Likert scale ranging from “very satisfied” to “very dissatisfied”. The items are calculated into the 6 subscales to assess satisfaction with life domains. The dimensions are scored by summing the scores for each item in the subscale. Possible total scores range from 16-112, where a lower score indicates worse quality of life demonstrated satisfactory psychometric properties in several studies [50,51]. The 6 subscales are as follows: (1) physical and material well-being; (2) personal development; (3) relationships with others; (4) participation in social activities; (5) participation in community and civic activities; and (6) recreation.The General Health Questionnaire (GHQ-12) is used to assess current mental health and psychological distress, reflecting the inability of normal functioning in regard to distressing experiences [52]. The questionnaire consists of 12 items on a Likert scale ranging from 0 to 3, where a higher sum-score indicates more symptoms of psychological distress and worse mental health. The GHQ-12 is widely used as a reliable screening instrument for psychological distress and minor psychiatric morbidity outside a clinical setting, showing high psychometric properties in various populations [52].The Self- Efficacy Parent Task - Short Form (SEPTI-SF) is used to measure 2 dimensions of the parent’s self-efficacy, discipline and achievement, showing satisfactory psychometric properties [53]. These dimensions consist of 11 quotes with 6 alternative answers from “highly disagree” (1) to “highly agree” (6). The dimensions are scored by summing the scores for each item in the subscale.The Dispositional Resilience Scale-Revised (DRS-15-R/Hardiness) is used to assess the parents’ hardiness in meeting challenging life events and situations [54]. The questionnaire consists of 15 quotes with 4 alternative answers scored on a Likert scale ranging from “highly disagree” (0) to “highly agree” (3). The items are summed into the 3 dimensions, commitment, challenge, and control, where a higher score indicate higher hardiness. The instrument is used internationally as well as in Norway, and has demonstrated validity and reliability within a wide range of studies as well as sensitivity to change [54].

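### Disease status and time since diagnosis are recorded before allocation, but neither the allocation nor the named t test uses them, and the eligibility wording is unclear for treated, disease-free parents

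*Protocol article*

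**What the plan says.** **Eligibility.** Under Eligibility Criteria, the healthy parent qualifies by being "a healthy parent having a partner or spouse diagnosed with cancer within the last five years and treated for cancer". The child criterion, joined to it by a conjunction, asks for a child aged 8 to 18 "living with a parent who has cancer". The only exclusion tied to the course of the illness is that "the ill parent has died". Recruitment contacts include "resource nurses in cancer care and palliation".

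**Links between illness course and outcome.** Previous Research names cancer severity among the factors that determine how children are affected. It says of families that "they often experience that help and support drop shortly after the diagnosis and their network withdraws".

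**Data in hand.** The healthy parent's questionnaire (Outcome Measurements) records "type and degree (metastasis) of cancer, months since diagnosis, type of treatment, and months of treatment and current treatment status". Trial Design says that consent and the T1 questionnaires come back first. Families are then assigned alternately by order of return, and no disease variable plays a part.

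**Analysis.** Power Calculations and Statistical Analyses names t tests and structural equation models for estimating the effect. Multiple regression is named for exploring relationships and testing the research model. No covariate is named for the comparison between arms.

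**The concern.** There are two linked points.

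First, a recruiter cannot tell from the text whether to enrol a family in which the parent was diagnosed within five years, has been treated and no longer has disease. The population to which the result applies is unclear to the same extent.

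Second, variables that the article treats as relevant to the outcomes are known for every family before assignment, and then appear in neither the allocation nor the stated effect estimate. In a trial of 60 families the arms can differ by chance in how many families are in active or advanced illness. Any difference in outcome between such families and the others then enters the arm comparison, and a plain t test cannot take it out. At stake is some precision, and how believable one observed difference is if the baseline table turns out uneven.

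**Working it through.** **Inputs from the article.** 30 families per arm, two-tailed alpha .05, target effect about 0.65 SD, power .80 (Power Calculations and Statistical Analyses). As of October 2015, 19 families had been allocated to intervention and 20 to control (Results).

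**Assumptions.** The article gives neither the stage mix nor the effect of stage. I take 20%, 30% or 50% of families in active or advanced illness. I take a gap of 0.3 to 0.8 SD between these and other families on the quantity analysed. Assignment is treated as unrelated to stage.

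**The plan's own figure.** With 30 per arm, a two-sided t test at .05 with power .80 detects 0.74 SD (0.72 by the normal approximation). Power at 0.65 SD is 0.70. The stated 0.65 reproduces only with a one-sided test (0.65 by t). That is a separate matter and the present point does not rest on it, but 0.70 is the right starting power below.

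**Chance imbalance in stage.** Let K = 60 × share. The number X falling in one arm is hypergeometric (60 families, K with the feature, 30 drawn). The arm gap is |2X − K|/30, so a gap of at least 20 points means |2X − K| ≥ 6.

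| Share | K | P(gap ≥ 20 points) |
|---|---|---|
| 20% | 12 | 0.104 |
| 30% | 18 | 0.158 |
| 50% | 30 | 0.196 |

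By symmetry, shares of 70% and 80% give the same results as 30% and 20%.

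**Imbalance in months since diagnosis.** If months are spread evenly over 0 to 60 (assumed), the SD is 60/√12 = 17.3. The SE of the difference in arm means is 17.3 × √(2/30) = 4.47 months, and 1.96 × 4.47 gives about ±8.8 months.

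**Effect on the comparison.** Shift = arm gap × stage gap. For a 20-point arm gap:
- 0.20 × 0.3 = 0.06 SD
- 0.20 × 0.8 = 0.16 SD

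The standard error of the arm difference is √(2/30) = 0.258 SD, so the shift is 0.06/0.258 = 0.23 to 0.16/0.258 = 0.62 standard errors.

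**Gain from adjustment.** With share q, gap g and within-stage SD 1, stage explains R² = q(1 − q)g² / [1 + q(1 − q)g²].
- Smallest case: 0.2 × 0.8 × 0.3² = 0.0144, so R² = 0.014.
- Largest case: 0.5 × 0.5 × 0.8² = 0.16, so R² = 0.138.

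The standardised effect becomes 0.65/√(1 − R²). Two-sided power moves from 0.697 to 0.703 in the smallest case and 0.760 in the largest. This does not deduct the degrees of freedom spent, so the smallest gain is practically nil.

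**Families still to be allocated.** 60 − (19 + 20) = 21.

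**The case against.** The case against most of this is good.

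- **The criteria do not conflict.** A reader might infer that the article contradicts itself on whether the parent must still have cancer. The criteria are cumulative and can both be met, and the present tense may simply be the article's general label for its population. What stands is an ambiguity for one kind of family.
- **The window runs from diagnosis.** It should not be read as treatment ended up to five years ago. Palliation appears only as the role of a recruitment contact, not as an eligibility rule.
- **Broad eligibility is deliberate.** The Discussion calls these families heterogeneous, describes irregular changes over years, and answers by tailoring the program. That is a legitimate choice, although tailoring does nothing for comparability between arms.
- **Late families are not shown to have nothing to gain.** Previous Research reports support lacking especially over time and a call for longer support, which argues for including them. Nor does any section say that outcomes will drift in stage-specific directions within 6 months; at most they may.
- **Chance imbalance is not bias.** If assignment is unrelated to stage, the t test's error rate already allows for it.
- **Covariates may be in an analysis plan that is not shown.** This is possible, and structural equation models could carry them. The point therefore rests only on what the article does state: a t test, which takes no covariates, as a named method for the effect.

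**Conclusion.** The point holds as a modest, inexpensive improvement in precision plus one wording reconciliation. It does not show that the trial is biased or that its population is wrongly chosen.

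Under the assumed shares of 20% to 50%, roughly one such trial in ten to one in five would have an arm gap of 20 points or more. A 20-point gap would move the estimate by 0.06 to 0.16 SD, well below the 0.65 SD target and less than one standard error. Adjustment raises power at 0.65 SD from 0.70 to at most about 0.76. All these figures depend on an assumed stage mix and stage effect. What comes from the article alone is that the variables are recorded before allocation, that it links severity and time since diagnosis to how families fare, and that neither the allocation nor the named t test uses them.

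**What to change.** 1. **Analysis.** For the between-arm effect, replace the unadjusted t test with a linear model containing arm, treatment status (active or palliative v completed) and months since diagnosis. Take both covariates from the T1 form, fix them before the data are examined, and apply them to all families, including the 39 already allocated. The cost is two degrees of freedom; no new data are needed.
2. **Eligibility wording.** Reconcile the phrases on disease status in the parent and child criteria, so that it is clear whether a family with a treated, disease-free parent is eligible. Which way to settle this is for the investigators. The cost is a text change.
3. **Optional.** Stratify by treatment status the families not yet allocated, at most 21 of 60. Under Ethical Implications and Risk, a protocol change has to be applied for to the ethics committee and the data services. With the covariates in the model the added benefit is small, so this need not be done.

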#### Recruitment

Participants are recruited nationwide using a wide-ranging recruiting strategy including information acquired through hospitals and primary healthcare, brochures, and different websites. Families are also recruited through the Norwegian Cancer Society, the Montebello Cancer Center, child responsible healthcare professionals in hospitals, cancer coordinators in primary healthcare, and resource nurses in cancer care and palliation.

#### Outcome Measurements and Data Collection

The literature recommends using a range of outcome measures in evaluating complex interventions, as a single outcome may not capture the results or unintended consequences of the study [47]. Therefore, different self-reported questionnaires are included for all participants, where social support, mental health, and quality of life are primary outcomes, while resilience and parent capacity are secondary outcomes.

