**Methods:**

A randomized controlled trial (RCT) in which families (N=60) living with parental cancer will be randomized to either an intervention group or a control group. The intervention will last for 3 hours and includes (1) introduction, (2) psycho-education (living with cancer in the family and the importance of social network support), and (3) discussion (this family’s need for social support). Primary outcomes are social support, mental health, and quality of life, and secondary outcomes are resilience and parental capacity. Data will be collected by a set of questionnaires distributed to healthy parents (N=60) living with a partner with cancer, one child in the family between 8-18 years of age (N=60), and network members (N=210) of the intervention families at inclusion, and after 3 and 6 months. Comparing differences between the intervention group (n=30) and the control group (n=30), the power analysis shows that *P*<.05 and a statistical power = .80 would detect effect sizes of clinical interest.

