
Information included in the questionnaire to the children.Demographic data: age, gender, siblings, and grade in schoolThe Revised Child Manifest Anxiety Scale (RCMAS) is used to measure anxiety reactions in children [55]. The RCMAS consists of 28 anxiety items and 9 lie (social desirability) yes-or-no items. Sum scores are provided for total anxiety and the 4 sub-scales: worry/oversensitivity, physiological anxiety, social concerns/concentration and a lie scale. A higher score indicates higher levels of anxiety or lie. RCMAS has demonstrated adequate psychometric properties [55].Kinder Lebensqualität (KINDL) is used to assess the quality of life of children [56]. KINDL consists of 30 quotes with 4 alternative answers ranging from “never” to “always”. The 6 subscales (physical health, emotional well-being, self-esteem, family, friends, and school) are calculated, where higher scores indicate higher QOL. The questionnaire has showed psychometrically acceptable values [56]. KINDL has 3 versions related to age, but since these cover the exact same questions with somewhat different wording, we decided to use Kid-KINDL to cover the entire age-span.

Information included in the questionnaire to the network.Questionnaire informationDemographic data: age, gender, education, social status, work affiliation, and relation to the family/sick parent.Assistance Questionnaire: Providers of support (AQP) represents the opposite version of AQR as it measures the social support given.GHQ-12, QOLS-N, Hardiness and CSS, as described for the healthy parents.

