##### Data Collection

Healthy parents and the children fill out the entire dataset at inclusion (T1), after 3 months (approximately one months after the intervention for the intervention group), and after 6 months (Figure 2). One of the two first authors provides the families with questionnaires by post and they return them to the researchers in pre-stamped envelopes. The social network members in the intervention group fill out the T1 questionnaires prior to the meeting starting. The network members in the intervention group fill out the same questionnaires after 3 (T2) and 6 months (T3), distributed via the Internet and the website SurveyMonkey.

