##### Power Calculations and Statistical Analyses

When comparing differences between the intervention group (n=30) and the control group (n=30), the power analysis showed that with *P*<.05 and a statistical power = .80, one would be able to detect effect sizes of *t* tests of about 0.65 of one standard deviation or higher [46]. This means an ability of detecting effects sizes of medium size or higher according to Cohen’s criteria [46]. This effect level was judged to be of clinical interest, and was within the study’s recruitment frame and economy.

All the data will be coded, verified, and entered into IBM SPSS Statistics for Windows Version 22.0. Normality will be assessed through examinations of skewness and kurtosis for all variables. A two-tailed *P* value of <.05 is considered to be statistically significant [46,57]. Descriptive statistics (mean/median or percentages, SD, and ranges) and correlation analyses (Pearson correlation) will be used to describe the data and to explore relationships among them [57]. The outcome variables will provide sum-scores on the interval level. Multiple regression analysis will be used to explore directional relationships among variables and testing the research model. For the estimation of the effect and the relationships of the variables relevant to the intervention, different methods such as *t* tests and structural equation (SEM) analyses will be used [57]. The missing data problem will be analyzed according to the questionnaires’ manual. Statistics will be reported in line with the SAMPL guidelines stated by Lang and Altman [58].

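### Three co-equal primary constructs, six instruments and two follow-ups share a general P<.05 threshold with no designated primary test, so if any significant result counts as success the false-positive risk is well above 5%

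*Protocol article*

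**What the plan says.** The abstract and the section Outcome Measurements and Data Collection name the same three primary constructs: "social support, mental health, and quality of life are primary outcomes, while resilience and parent capacity are secondary outcomes". The second of these defends having several, on the ground that "a single outcome may not capture the results or unintended consequences of the study".

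The Outcome Measurements section then gives the instruments. For the healthy parent, "The Crisis Support Scale (CSS) [48] and the Assistance Questionnaire-Receivers of support (AQR) [49] measure social support"; GHQ-12 covers mental health; and "The Quality of Life Scale (QOLS-N) is used to measure" quality of life. The child completes RCMAS (anxiety) and KINDL (quality of life). For KINDL the article describes only subscales: "The 6 subscales (physical health, emotional well-being, self-esteem, family, friends, and school) are calculated".

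Under Data Collection, parents and children "fill out the entire dataset at inclusion (T1), after 3 months", and again after 6 months.

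Power Calculations and Statistical Analyses sets one general rule: a two-tailed P "value of <.05 is considered to be statistically significant". It says that effects will be estimated by several methods, with t tests and SEM as examples. Its power statement is for a t test with 30 per arm, 80% power and a detectable effect of about 0.65 SD, and it names no outcome. The article names no primary instrument, respondent or time point, and gives no order of testing.

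**The concern.** A trial needs one result, or one stated rule for combining results, that decides whether its main hypothesis is supported. Here the article makes three constructs equal, gives one of them two instruments, measures two of them in two respondents, and repeats everything at two follow-ups. A reader who follows it as written cannot tell which comparison decides.

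If any one significant result is enough, the false-positive risk is several times the nominal 5%. If all are needed, power falls below the 80% stated for a single test. This matters because the Discussion says that guidelines for the local healthcare system will follow if the results are successful, and at least six papers are planned.

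**Working it through.** **Inputs**
- Primary constructs: 3 (abstract; Outcome Measurements and Data Collection).
- Instruments in the randomized families: parent CSS, AQR, GHQ-12, QOLS-N; child RCMAS, KINDL. Total 6 (Outcome Measurements). Placing RCMAS under mental health and KINDL under quality of life is inferred from the hypotheses, the research model and the description of each scale; the article has no table that does it.
- Post-baseline times: 2, at 3 and 6 months (Data Collection).
- Alpha .05 two-tailed; 30 per arm (Power Calculations and Statistical Analyses).
- Correlations: none are given. Those below are assumptions.
- Network members are measured only for intervention families, so their scales add no comparison between arms.

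**The plan's own figure**

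Detectable effect, normal approximation: (1.960 + 0.842) × √(2/30) = 2.802 × 0.258 = 0.72 SD. The noncentral t calculation gives 0.74 SD two-sided. At 0.65 SD the two-sided t test has about 70% power. The stated 0.65 SD is reproduced only one-sided (0.650 SD), against the two-tailed rule in the same section. So 0.74 SD is the baseline for any comparison below.

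**Number of comparisons**

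6 instruments × 2 times = 12 comparisons between arms, without subscales.

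**Chance of at least one P<.05 under no effect**

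Independent tests, 1 − 0.95^k:
- k = 3: 1 − 0.857 = 14.3%
- k = 6: 1 − 0.735 = 26.5%
- k = 12: 1 − 0.540 = 46.0%

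Correlated tests, multivariate-normal simulation (200,000 draws or more) of any |z| > 1.96:

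| Tests | r = 0.3 between instruments | r = 0.5 between instruments |
|---|---|---|
| 3 (one per construct) | 13.6% | 12.5% |
| 6 instruments, one time | 24% | 21% |
| 6 instruments, two times (0.6 between times) | 39% | 34% |

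Sensitivity for 12 tests: letting the parent–child correlation be lower (0.1–0.3), within-person 0.3–0.7 and between times 0.5–0.8 gives 29% to 41%. With one common correlation for all 12 tests, the rate is 23% at 0.7 and 19% at 0.8.

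**Cost of a Bonferroni split instead**

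Over six tests alpha is .05/6 = .0083. The two-sided detectable effect rises from 0.74 to 0.93 SD, and power at 0.65 SD falls from about 70% to 42%.

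**The case against.** The document is a journal article and the analysis plan is not shown. Testing order, priority of time points and multiplicity adjustment are often left to that plan. This has weight, and silence on adjustment alone would not be a finding. But the article does fix the primary outcomes: it names three as equal, defends the choice, attaches a flat .05 threshold and powers one test. The point concerns what those statements do together.

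The stated preference for a range of outcomes is reasonable for a complex intervention. It justifies measuring several things; it does not require that all be equally primary.

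A reader might infer that the plan commits to 12 separate primary t tests. It does not. The .05 rule is a general convention, and SEM or regression could pool outcomes or times. Twelve is the count if each instrument is compared at each follow-up, which is why smaller families are shown too. A reader might also quote 46% as the error rate. That needs 12 independent tests, which is implausible for repeated scales from the same people and families.

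Counting every subscale would overstate the case. The nine support types in AQR are not defined as nine scores, and one RCMAS subscale is a lie scale. Neither is counted here.

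Finally, the hypotheses only partly dictate a primary test. CSS and AQR stand side by side for social support, and nothing ranks GHQ-12 against QOLS-N, KINDL against RCMAS, or 3 against 6 months. That choice belongs to the sponsor.

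**Conclusion.** The concern holds: the article fixes co-equal primaries and one flat threshold without a deciding test. Under no effect, and if any significant result counts as success, the false-positive chance is about 13–14% with one test per construct, 21–26% for six instruments at one time, and 34–39% for six at two times under the assumed correlations. Even the smallest of these is about two and a half times the nominal 5%.

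The figures rest on three assumptions: that one positive result suffices, that each instrument is compared separately, and that the correlations are as stated. A single joint test named as primary would lower them, but the article names none. The documents do not show that such a claim will be made; they leave it open.

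**What to change.** Before outcomes are compared by arm, designate one primary instrument, respondent and time point. Healthy-parent CSS total at 6 months (T3) is a natural candidate: it has a defined total score and addresses hypothesis 1. Another choice is acceptable if it is justified.

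Then test the remaining primary constructs in a prespecified fixed order following hypotheses 1 to 3: parent GHQ-12 and QOLS-N total, then the child outcomes. Each is tested at two-tailed .05, and only while the previous test is significant. Name in advance a single KINDL score, since the article describes only subscales, and the RCMAS total anxiety score. Report AQR, all subscales and the other time point as secondary, with confidence intervals and no confirmatory claim. Tie the power statement to the designated test.

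Submit this as a protocol change to the ethics and data bodies, as the section Ethical Implications and Risk requires. The article reports 45 families enrolled by October 2015 and expects first results that month. If any comparison by arm has already been made, say so and label the results accordingly.

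Cost: wording and one submission. Later outcomes lose confirmatory status if an earlier one fails. The first test keeps full alpha, but with 30 per arm it detects about 0.74 SD two-sided (about 70% power at 0.65 SD). Bonferroni over six would raise that to about 0.93 SD, so the ordered sequence is the cheaper route.
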